## Abstract

**Background:**

Numerous studies suggest that exercise may be an effective adjunct treatment for substance use disorders. It has been suggested that exercise-induced improvements in inhibitory control may reduce craving for the substance of abuse. However, this potential mechanism has seldom been researched.

**Objectives:**

The aim of the ExAlCo Study is to examine how acute bouts of exercise, at varying intensities, impact on craving for cocaine or alcohol. Cerebral haemodynamic responses during cognitive tests of inhibitory control, and exposure to substance-related cue imagery, will also be assessed using functional near-infrared spectroscopy.

**Design:**

The study is a crossover randomised controlled trial. Participants will be recruited from inpatient and outpatient psychiatric treatment centres, on the approval of their treating physician. A healthy control group will be recruited using online advertising. All participants will undergo each of three conditions in randomised order: 20 min of cycle ergometry at 50–60% of maximum heart rate; 20 min of exercise at 70–80% of maximum heart rate; and 20 min of quiet reading. Immediately before and after each condition, participants will be asked to complete a computerised Stroop test, watch a film containing substance-related images and self-report craving levels. During the Stroop test and film viewing, participants’ neural activity will be measured via functional near-infrared spectroscopy.

**Outcomes:**

The primary outcome measures are self-reported craving, inhibitory control and cerebral haemodynamic response to the Stroop test and a substance-related film. It is hoped that the findings from this study will shed more light on the role of exercise in the treatment of substance use disorders, particularly its scope in preventing relapse through reduced craving severity.

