### Statistics

Sample size is calculated a priori using G*Power 3.1 [58]. Based on effect sizes reported in previous studies [25, 40] and an alpha level set to 0.05, the initial power analysis indicates that 17 participants per group are required to reach 85% statistical power. As drop-outs have to be expected, the sample size is increased to 20 participants per group. Note that the power analysis is based on the acute effects of moderate aerobic exercise on prefrontal cortex activity and inhibitory control. The statistical analysis of collected data is performed with SPSS 23.0 (IBM Statistics, USA) for Windows. Acute effects of exercise on inhibitory control and HbO_2_ concentration are examined using a 2 (group: alcohol dependent, healthy controls) × 3 (condition: control, moderate exercise, highly intense exercise) × 2 (time: pre, post) ANOVA on reaction time and the haemodynamic response to incompatible trials of the Stroop colour–word test. Additionally, effects of exercise on cue-elicited craving and HbO_2_ concentration (neutral cues subtracted from alcohol/cocaine cues) are investigated by applying a 2 (group) × 3 (condition) × 2 (time) ANOVA. Main effects and interactions are reported. Subsequently, Bonferroni-corrected *t* tests are used to decompose any significant interactions. The level of statistical significance is set to *p* < 0.05. Data from participants who do not complete all three measurement points will not be used.

Regarding missing data, as participants who do not complete all three sessions will be excluded from the study, it is anticipated that missing data will chiefly be due to faults in the fNIRS and Stroop programming, and thus will be missing at random. For this reason, multiple imputation will be used to address this issue.

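### Four unranked primary outcomes are each tested at 0.05 with no adjustment across them, the hypothesised contrasts are reached only through an omnibus gate, and the stated 85% power does not cover craving

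*Protocol article*

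**What the plan says.** **Outcomes.** The Abstract (Outcomes) says: "The primary outcome measures are self-reported craving, inhibitory control and cerebral haemodynamic response to the Stroop test and a substance-related film". This gives four measures: self-reported craving, Stroop performance, HbO2 response to the Stroop test and HbO2 response to the film. None is ranked above another.

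**Analysis.** Methods, Statistics specifies 2 (group) × 3 (condition) × 2 (time) ANOVAs. It adds "Main effects and interactions are reported", and "The level of statistical significance is set to" p < 0.05. Bonferroni-corrected t tests come next, only to break down an interaction that has reached significance.

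**Hypotheses.** The end of the Background sets out two families, both within dependent participants: moderate exercise against passive control, and intense exercise against passive control. Each covers the same four measures.

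**Power.** Statistics gives "an alpha level set to 0.05, the initial power analysis indicates that 17 participants per group are required to reach 85% statistical power". The effect sizes are given only by reference to two earlier studies. The section limits the claim itself: "Note that the power analysis is based on the acute effects of moderate aerobic exercise on prefrontal cortex activity and inhibitory control". It then allows for attrition: "As drop-outs have to be expected, the sample size is increased to 20 participants per group".

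**The concern.** There are two separate problems, and both follow from rules the article fixes.

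The first is multiplicity across outcomes. Any of the four primary outcomes can reach p < 0.05, and no rule says which result, or how many, would support the trial's claim. The Bonferroni step works within one outcome's follow-up tests and does nothing across outcomes.

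The second is that the analysis does not test the hypotheses directly. They are single contrasts within patients. The ANOVA interactions pool those contrasts with the other exercise intensity and with healthy controls, who are not expected to respond to the substance cues. A real effect of moderate exercise in patients must pass that pooled test and then a corrected t test. The power statement does not describe this route. It also leaves out craving, which the Abstract (Objectives) makes the aim of the study.

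**Working it through.** **1. The plan's own figure.** The article gives no effect size, G*Power test family or correlation among repeated measures, so 17 per group cannot be reproduced. It is attainable: a two-sided paired t test with a standardised difference of 0.8 needs n = 17 for 85% power at 0.05. The attrition step is consistent with a 15% allowance: 17/(1 − 0.15) = 20.

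Solving backwards for the effect with 85% power at n = 17 and alpha 0.05:

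| Assumed test | Implied effect |
|---|---|
| Paired t, two-sided | 0.774 SD of the paired difference |
| Paired t, one-sided | 0.680 |
| Independent t, two-sided | 1.06 |
| Repeated-measures F, one group, 3 measures (correlation 0.5 assumed) | f = 0.343 |
| 2 × 3 interaction, N = 34 (correlation 0.5 assumed) | f = 0.237 |

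The power figures in steps 3 and 4 use the first row, because it matches the hypothesised contrast. This is an assumption; the article does not state it.

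**2. Error across outcomes.** For m independent tests at 0.05, family-wise error = 1 − 0.95^m.

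- One test per outcome, m = 4: 1 − 0.95^4 = 18.5%.
- Condition × time and group × condition × time for each outcome, m = 8: 1 − 0.95^8 = 33.7%.
- Four tests with correlated outcomes: 17.4%, 15.5% and 11.3% at correlations 0.3, 0.5 and 0.8.

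The gate and Bonferroni do restrain error within an outcome. In simulation under the full null, the chance of any significant gated t test among patients is about 2.5% per outcome. Over four independent outcomes that is 1 − (1 − 0.025)^4 = 9.6%, about 10%.

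**3. Power of the gated route.** The simulation used post-minus-pre changes in one patient group and one control group, with compound symmetry, a moderate-exercise effect of 0.77 SD and no intense-exercise effect. The gate is either relevant interaction at 0.05, followed by t tests at 0.05/3.

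| Moderate versus rest in patients | n = 17 | n = 20 |
|---|---|---|
| Direct paired test at 0.05 | 85% | 91% |
| Paired test at 0.05/3, no gate | 69.5% | 78.9% |
| Gate then 0.05/3, only patients respond | 66% | 76% |
| Gate then 0.05/3, controls respond equally | 69% | 79% |
| Only the three-way interaction opens the gate, only patients respond | 51% | 61% |

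Most of the loss from 85% comes from the Bonferroni step. The gate adds about 3 points when either interaction can open it, and considerably more when only the three-way interaction can. In that last case, if controls respond as patients do, the contrast is reached only 3% of the time at n = 17.

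**4. Power of a planned contrast without the gate.** With the same 0.774 SD and a two-sided paired t test:

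- At 0.05/4 = 0.0125: 65% at n = 17 and 75% at n = 20. Family-wise error over four independent tests is 1 − 0.9875^4 = 4.9%.
- At 0.05/8 (for example four outcomes in two patient groups): about 53% at n = 17 and 65% at n = 20.

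For one contrast per outcome in one patient group, control over all four outcomes therefore costs almost nothing against the present route (65% against 66% at n = 17).

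**The case against.** The strongest reply has four parts.

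**The article does correct for multiple testing.** This is true of the follow-up t tests. A reader might infer that false positives are wholly uncontrolled, and the text does not support that: the gate and Bonferroni hold error within an outcome to about 2.5%. The gap is across outcomes. Nor does the gate create false positives; it lowers them and costs power.

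**The family should not be inflated.** A reader might count all seven ANOVA effects for four outcomes and reach 1 − 0.95^28 = 76%. That count includes main effects that test no stated hypothesis and are merely reported. It also presumes that all four outcomes have such an ANOVA. For self-reported craving this is not certain, because Statistics names cue-elicited craving, a term that the section on fNIRS recordings uses for HbO2 difference waveforms. The fair figures are 18.5% and 34%, and both are upper values because the outcomes come from the same people in the same sessions.

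**The 85% is not shown to be wrong.** This stands. Statistics restricts it to moderate exercise, prefrontal activity and inhibitory control, and never claims it for craving. With test and effect size unstated, it may be correct for an ANOVA F test on those measures. A reader might infer that the figure is invalid; the documents show only that it does not extend to craving or intense exercise, and they do not show that it holds for gated, corrected contrasts.

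**A hierarchy can be left to an analysis plan, and the study is mechanistic.** This has some force, since no passage says that one positive outcome would make the trial positive. But the article itself fixes the significance level, the models, the reach of the Bonferroni correction and the order of testing. Followed as written, those rules give no control across outcomes.

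**Conclusion.** The point holds in a limited form. Four unranked primary outcomes are tested at 0.05 with no adjustment across them. Family-wise error is at most 18.5%, or 34% counting both relevant interactions, if the outcomes are independent; at a correlation of 0.5 the first figure is 15.5%. The hypothesised contrasts have no direct test. The loss of power on the gated route, from 85% to about 66% at n = 17 and from 91% to 76% at n = 20, depends on an assumed paired effect of 0.77 SD, compound symmetry and a response in patients only. The article confirms none of these. That craving and intense exercise fall outside the power statement needs no assumption, because the Statistics section says what the calculation was based on.

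This should be corrected before analysis. It does not mean that the sample size is wrong or that any single test is invalid.

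**What to change.** 1. Pre-specify two contrasts of pre-to-post change within patients, moderate versus rest and intense versus rest, not conditional on an omnibus F.
2. Control error over the four primary outcomes in one family: Holm, a fixed order, or a single primary outcome. The choice is the authors'; craving would match the stated aim. Separate families at 5% each would not hold 5% overall. Count both patient groups if they are tested separately, and say where the intense-exercise contrasts sit in the scheme.
3. Say explicitly which analysis applies to self-reported craving.
4. Keep the full ANOVA as a supportive analysis.
5. Restate the power sentence: the 85% applies only to an unadjusted test on prefrontal activity and inhibitory control. Give the effect size and test used, and add the detectable craving effect at n = 17 at the chosen significance level. For a two-sided paired test at unadjusted 0.05 and 85% power, that effect is 0.77 SD of the paired difference.

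The cost is wording only, with no new participants or measurements. The stated power becomes less favourable: under the assumed 0.77 SD, 65% at 0.05/4 and about 53% at 0.05/8 with n = 17. The second figure is below the 66% of the present route, so testing both patient groups separately on all four outcomes has a real price. That is an argument for a fixed order or a single primary outcome.

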**Trial registration:**

ClinicalTrials.gov, NCT03502486. Registered retrospectively on 5 April 2018.

**Electronic supplementary material:**

The online version of this article (10.1186/s13063-018-3062-0) contains supplementary material, which is available to authorized users.

## Background

Craving substances to which an individual has developed dependence is one of the most troubling symptoms of addiction, and is frequently reported by sufferers to lead to relapse following a period of abstinence [1]. This holds true for cocaine-dependent [2] and alcohol-dependent [3] individuals. Craving for a substance is therefore a subject of great importance in addiction research and can be assessed in a number of ways, frequently via exposing the individual to the substance of dependence, or its image or scent, a so-called “cue” [4]. Alcohol-dependent and cocaine-dependent individuals reliably report enhanced craving and display physiological reactivity to their respective substance cues [5, 6].

Neuroimaging techniques are frequently used to examine the areas of the brain which are involved in the experience of craving [7, 8]. Because craving is an important outcome in addiction treatment, insight into functional brain activity serves to guide treatment innovations and improve understanding of the physiological substrates of addictive behaviour [9]. While a number of brain regions are implicated in cue reactivity and craving, there has been a growing focus on the prefrontal region of the outer cortex [7, 10]. Bonson et al. [11] assessed neural activity in response to cocaine cues in cocaine-dependent individuals, and determined that increased activation of the lateral orbitofrontal cortex and dorsolateral prefrontal cortex correlated with craving. Similarly, Grüsser et al. [12] reported activation of the medial prefrontal cortex in abstinent alcoholics following exposure to alcohol cues, with more intense activation observed in those who subsequently relapsed.

The prefrontal cortical region is also implicated in a number of cognitive processes, including inhibitory control [13]. Inhibitory control is a core component of executive function, and is defined as the ability to control one’s attention, behaviour and thoughts, and to override an internal predisposition or ignore external stimuli [14]. Crucially, inhibitory control has also been shown to be a relevant parameter in the understanding of craving, as it constitutes the ability to control a reaction upon exposure to the craved substance [15]. For example, Goldstein and Volkow [16] report that the activation of the orbitofrontal cortex observed during craving is associated with reward reinforcement, but also with deficits in inhibitory control. The ability to exercise inhibitory control during exposure to cocaine cues has been shown to rely in part on normal functioning of the prefrontal cortex [17]. Neural functioning in the prefrontal cortex therefore appears to be relevant to the phenomenon of craving, and inhibitory control may be a moderating factor [18].

A number of techniques can be used to produce images of prefrontal cortical activity. Functional magnetic resonance imaging (fMRI) enables imaging of deep brain structures, and allows for highly accurate spatial localisation of brain activity. However, the method has two chief limitations. First, fMRI requires the participant to lie, without moving, during the imaging process; consequently, it is unclear how apparent reductions in craving in this rather unnatural state will translate to craving experienced in a more normal setting. Second, fMRI must be carried out in a specialist laboratory, and the machine itself is large and extremely costly. Hence, it cannot be expected that findings from fMRI studies can be easily translated to the practice of non-hospital-based addiction treatment services [19]. By contrast, functional near-infrared spectroscopy (fNIRS) is a portable, wearable imaging device, which is much less susceptible to movement artefacts [20]. Both imaging systems identify neural activity by monitoring changes in the concentration of blood oxygen levels in various brain regions [21]. As fNIRS is mainly suited to assessing neural activity in the outer cortex of the brain, for studies focusing on cognitive functions it represents an affordable, portable means of assessment. As the device can be positioned on the head within 2 min, and does not require the application of conductive gel, it is also more time efficient than EEG. These properties of fNIRS mean that, if it proves a useful tool in the assessment of craving severity in addiction, it can be incorporated into clinical practice with comparative simplicity [22].

For the purposes of the present study, assessing neural activity during exposure to substance cues permits a physiological assessment of cue reactivity to accompany craving self-report, a measure which, on its own, may be subject to social desirability bias [23]. The fNIRS assessment during the Stroop test provides additional information on the processes underlying impaired or successful inhibitory control. Given that previous studies have linked exercise-induced benefits with prefrontal cortex function [24, 25], an examination of the cerebral haemodynamic response to the cognitive task may also allow deeper insights into the mechanisms by which exercise benefits inhibitory control in patients undergoing therapy for alcohol addiction and healthy adults.

fNIRS has already been used to assess brain activity in alcohol-dependent individuals. Ernst et al. [26] reported decreased concentration of deoxygenated haemoglobin (HHb) in the right dorsolateral prefrontal cortex during an approach-avoidance task, and increased concentration of oxygenated haemoglobin (HbO_2_) in the left anterior lateral orbitofrontal cortex in response to image cues. Schecklmann et al. [27] reported reduced activation in the frontotemporal region during a cognitive task. Importantly for the purposes of the present study, Bunce et al. [28] have used fNIRS imaging to show enhanced responses to alcohol cues in non-treatment-seeking alcohol-dependent patients (compared to social drinkers). In the sole study to examine craving for alcohol and cocaine, discussed in detail in the following, Grandjean da Costa et al. [29] found exercise-induced increases in oxygenated blood concentrations in the prefrontal cortex compared to baseline, accompanied by lower craving scores. Increases in oxygenation were, however, less pronounced than those in healthy controls.

Central to the focus of the present study, acute exercise has been shown to influence activity in the prefrontal cortex. In both men and women, cortical activity measured with electroencephalography has been found to increase across different regions from warm-up to moderate cycling exercise, but decreases in frontal regions with prolonged duration [30, 31]. Additionally, prefrontal cortex activity during exercise is affected by intensity as submaximal to maximal loads elicit a decrease in the oxygenation of the prefrontal cortex [32]. Due to the exercise-induced modulation of prefrontal cortex function, it can therefore be speculated that exercise may influence craving.

Exercise has increasingly been examined as a potential adjunct therapy in addiction treatment [33]. While most research has focused on the effects of multi-session exercise interventions, some studies have shown promising results of acute exercise bouts on addiction-related outcomes. In this respect, acute bouts of exercise have been shown to both reduce perceived craving and increase inhibitory control in methamphetamine-dependent individuals [18]. To date, evidence for exercise in alcohol dependence is weaker than for other substances [33, 34]. The reason for this discrepancy is not clear [35].

A potential underlying mechanism of exercise-induced reductions in craving might be an increase in inhibitory control after exercise. A recent meta-analysis of 40 studies has reported small to moderate effects of moderately intense aerobic exercise on inhibitory control and other components of executive functioning in healthy populations. The effects were independent of fitness levels, so that athletes and non-athletes can expect similar benefits [36]. Investigating further moderators with meta-regression, Chang et al. [37] have found that aerobic exercise bouts lasting 11–20 min elicit greater benefits for executive function than longer or shorter durations. Finally, Everitt [38] has identified an association between prefrontal cortical inhibitory control and extinction; that is, improved inhibitory control is associated with reduced cue-elicited craving. fNIRS studies with healthy adults were able to show that increased improved inhibitory control following aerobic exercise at mild to moderate intensity is associated with increased activation of the prefrontal cortex and the dorsolateral area in particular [25, 39]. In contrast, a decrease of the HbO_2_ concentration during highly intense aerobic exercise has been found to be correlated with slowing of reaction time on an inhibitory control task [40]. It therefore seems that fNIRS is an appropriate method for examining the potential effects of exercise on cue-elicited craving and inhibitory control.

To date, one study has examined the effect of an acute exercise bout on cocaine and alcohol craving, and has employed fNIRS during a test of inhibitory control to examine whether this may be a moderating factor. Grandjean da Costa et al. [29] reported reductions in cravings for alcohol or cocaine following a maximal exercise test; however, no significant improvements in reaction time on the Stroop test were observed. While this study is an important initial step in exploring whether, and to what extent, exercise-induced reductions in craving occur, and are moderated by inhibitory control, two aspects of the study design might obscure certain effects. First, an incremental maximal exercise test was used as the acute exercise bout; this means that all participants increased their exercise intensity from easy, through moderate to very intense, in a single unbroken sequence, and completed the craving assessment only before and after the entire bout. This means that it is impossible to tell what effect intense exercise has on craving, as the reported reductions may simply carry over from the moderate intensity preceded it. Second, the tests of inhibitory control were carried out repeatedly during the exercise test. While this enabled the researchers to obtain results at varying intensities, it is at least possible that the challenge of combining exercise (particularly at high intensities) with the task may have affected the results. It must also be noted that this study therefore suggests that exercising may reduce craving, and does not address the related but equally important question of whether craving following exercise is reduced.

In summary, there is evidence that craving in alcohol or cocaine-dependent individuals can be reliably elicited by exposure to images, and that craving correlates with specific activation patterns in regions of the prefrontal cortex. The activation of these regions can be imaged using fNIRS. Inhibitory control may moderate craving, and activation during inhibitory control tasks can also be imaged using fNIRS. Finally, during an acute bout of exercise, activity in the prefrontal cortex increases (at moderate intensities) and decreases (at high intensities), and acute exercise has been shown to influence both inhibitory control and craving. While the evidence for exercise in general is weaker for alcohol than for cocaine dependence, the single study to date to examine the effects of acute bouts on craving found reductions for both substances. Consequently, the aim of this study is to examine whether, following acute exercise bouts at moderate and high intensities, reduced craving and increased inhibitory control can be observed in alcohol or cocaine-dependent individuals. As the focus of this study is the potential of exercise to be integrated into treatment, individuals in treatment for their dependence, who have been abstinent for a short period, will be recruited.

Based on the state of research to date, we propose the following hypotheses:In alcohol-dependent and cocaine-dependent participants, compared to a passive control condition, a bout of moderate exercise will:reduce self-reported craving;improve behavioural performance on the Stroop test;elicit increased activity in the prefrontal cortex during the Stroop test; andbe followed by decreased activity in the prefrontal cortex during exposure to substance-related cues.

